## Abstract

Obstructive sleep apnea (OSA) is the most common sleep-related breathing disorder and is increasingly recognized as a contributor to cognitive decline and a potential risk factor for neurodegeneration. Previous studies have also identified various associated comorbidities such as vascular dysfunction, metabolic alterations, and neuroinflammatory changes. Positive airway pressure (PAP) therapy has been associated with cognitive improvement in some studies, but its long-term effects on cognitive function remain uncertain. This study employs a prospective, observational, longitudinal cohort design to examine longitudinal associations between disease severity, PAP therapy and cognition. Additionally, we aim to examine the relationships between cognitive dysfunction, brain structure and associated OSA-related risk factors. A total of 100 eligible participants with mild to severe OSA will be recruited. All participants will undergo comprehensive assessments at baseline and after 12 months, including neurological, pulmonary, and ear, nose and throat clinical examinations, polysomnography, neuropsychological testing, brain magnetic resonance imaging with volumetry, anthropometric measurements, blood and saliva sampling for the assessment of the selected laboratory parameters, gut microbiome analysis, and evaluation of endothelial function and baroreflex sensitivity. This study may improve understanding of how PAP therapy and OSA-related pathophysiological processes influence cognitive outcomes.

## 1. Introduction

Obstructive sleep apnea (OSA) is a multifaceted sleep disorder characterized by repeated episodes of upper airway obstruction during sleep, leading to significant reductions in airflow and oxygenation. This condition manifests as complete cessation of breathing (apneas) lasting 10 s or more, or partial obstructions (hypopneas) that result in reduced airflow [1,2]. Beyond its primary respiratory manifestations, OSA is associated with major comorbidities such as cardiovascular, metabolic, and neurocognitive disorders, affecting overall health and quality of life [3,4,5,6]. Recent research has also begun to focus on the interplay between OSA and biomarker-related susceptibility to neurodegeneration, particularly highlighting associations with the apolipoprotein E (ApoE) ε4 allele and plasma neurofilament light chain (pNfL) levels. The presence of the ApoE ε4 allele has been linked to increased vulnerability to OSA-related cognitive decline [7,8,9], while elevated levels of pNfL may indicate axonal injury and neurodegeneration in affected individuals [10,11,12].

With the global rise in dementia and aging populations, identifying modifiable contributors to cognitive decline is critical [13]. OSA affects nearly one billion people globally, yet remains underdiagnosed—particularly in older adults, where its cognitive effects may overlap with or accelerate early neurodegenerative changes [14,15,16]. As a treatable condition, OSA may play a key role in preventing or delaying cognitive impairment in vulnerable populations.

While a number of studies have examined the effects of positive airway pressure (PAP) therapy on cognitive function and brain structure [17,18,19], to our knowledge no study to date has explored the full range of comorbidities and biological mechanisms relevant to cognitive outcomes in OSA. Moreover, most existing studies have used brief screening tools, limiting sensitivity to subtle or domain-specific impairments in OSA. This limited scope has constrained our understanding of the complex, multifactorial effects of PAP therapy on the brain. In this study, we aim to provide a detailed description of the cognitive profile, investigate the association between disease severity, PAP therapy and cognition, and explore the relationships between OSA and its contributing factors.

## 2. Materials and Methods

The design of this study protocol was developed in accordance with the STROBE guidelines [20] for observational studies. Selected elements of the SPIRIT 2013 guidelines [21] were also considered where applicable. This study was registered on ClinicalTrials.gov (Identifier: NCT07364318).

### 2.1. Study Aims and Hypotheses

The primary aim of this study is to perform a detailed cognitive assessment in patients with OSA. We aim to analyze the baseline prevalence, severity, and pattern of cognitive deficits in this population and to evaluate changes in cognitive function after 12 months of PAP therapy to gain a clearer understanding of the initial cognitive status from which potential therapeutic or disease-related changes may occur.

The secondary aims of this study are exploratory. We plan to investigate associations between cognitive outcomes and a broad spectrum of OSA-related measures, including polysomnography (PSG)-derived sleep parameters, brain volumetric measures, anthropometric and metabolic indicators, biomarkers (e.g., pNfL, oxidative stress markers, lipid subfractions, ApoE genotype), gut microbiome composition, vascular function, and autonomic nervous system regulation. We also aim to explore how PAP adherence relates to longitudinal changes in these cognitive and physiological outcomes.

### 2.2. Study Design and Setting

This study employs a prospective, observational, longitudinal cohort design, conducted at the Sleep Laboratory of the 1st Department of Neurology, Faculty of Medicine, Comenius University, University Hospital Bratislava, Slovakia. The study will enroll at least 100 eligible participants with newly diagnosed mild to severe OSA, who have no history of chronic diseases (except for overweight and obesity) and are not receiving any chronic medication. The Sleep Laboratory has active research programs on sleep disorders, an established infrastructure for clinical studies, and a high volume of patient referrals. Participants meeting all inclusion criteria will receive detailed information about the purpose and procedures of the study before enrollment.

Diagnosis of OSA must first be confirmed by overnight PSG. Participants will then enter the cohort after meeting the inclusion/exclusion criteria described below. Trained research personnel will obtain informed consent from the patient after providing all the necessary information. Cognitive function, OSA-related measures (PSG variables), sleep parameters, brain magnetic resonance imaging (MRI) and volumetric measures, anthropometric parameters, blood and saliva biomarkers, gut microbiota composition, endothelial function, and baroreflex sensitivity will be assessed at baseline and after 12 months, together with neurological, pulmonary, and ear, nose, and throat (ENT) examinations. Those patients who are routinely clinically indicated for PAP therapy will receive treatment, and their adherence will be monitored throughout the study. PAP therapy is prescribed exclusively based on routine clinical indications and follows standard-of-care pathways. The study protocol does not mandate initiation, modification, or discontinuation of PAP therapy and does not include any study-driven therapeutic decision-making. Participants are not randomized to treatment groups, and no experimental group allocation is performed. Blinding of participants and investigators to PAP therapy status is not feasible due to the nature of the study design. Participants are invited to contact the principal investigator at any time to inquire about results. The general study timeline is described in Table 1.

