#### 2.5.2. Secondary Outcome Measures

##### Changes in Baseline Measures

After 12 months of PAP treatment, patients will undergo the same assessments as during their initial hospitalization (besides ApoE genotyping), following the original protocol. This will include overnight PSG, neuropsychological testing, brain imaging, brain volumetry, anthropometric measurements, blood and saliva samples, gut microbiome, vascular functions and baroreflex sensitivity assessments. All collected data will be compared with baseline values, allowing us to explore the associations between PAP therapy and changes in cognitive and other selected parameters. All secondary analyses are considered exploratory and hypothesis-generating.

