#### 2.5.3. Exposure Variables of Interest

##### PAP Therapy and Adherence to Treatment

The gold standard treatment of moderate/severe OSA is positive airway pressure (PAP) therapy, which works by holding the airway open using a pneumatic splint. There is evidence to suggest that compliant PAP therapy use can have beneficial effects on some of the consequences of this disorder. Adherence to the treatment will be measured through an adherence tracking system using smart memory cards, which will report all needed parameters. Adherence will be primarily analyzed as a continuous variable (e.g., average hours of use per night) to capture potential dose–response relationships with cognitive outcomes. In addition, secondary analyses will examine adherence as a categorical variable using standard criteria to classify participants as adherent or non-adherent (e.g., ≥4 h of use per night [23]), allowing for clinically interpretable group comparisons. To promote participant retention and complete follow-up, study assessments are scheduled in alignment with routine clinical visits where feasible.

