### 2.7. Data Analysis Plan

Descriptive statistics will be used to summarize demographic and clinical characteristics. The normality of continuous variables will be assessed using visual inspection (Q–Q plots, histograms) and statistical tests (e.g., Shapiro–Wilk). Continuous variables will be presented as mean ± SD for normally distributed data or median with interquartile range for non-normally distributed data. Categorical variables will be expressed as frequencies and percentages.

Primary analyses will evaluate within-subject changes in cognitive function over the 12-month period (i.e., change scores ΔT12–T0). These changes will be analyzed using linear mixed-effects models with a random intercept, which allow for repeated measurements and account for inter-individual variability. Fixed effects will include time, PAP adherence, and covariates such as age, sex, and education. An interaction term between time and adherence will be used to assess whether longitudinal changes differ according to adherence level.

Secondary analyses will explore associations between changes in cognitive outcomes and other measured variables, including sleep parameters, volumetric measures, anthropometric and metabolic indicators, biomarkers, and other selected laboratory measures (e.g., pNfL, ApoE genotype, gut microbiome composition), as well as indices of vascular health and autonomic nervous system function. These associations will be examined using Pearson or Spearman correlations between change scores (ΔT12–T0) and multiple linear regression models with a limited number of predictors (maximum of 4 per model) to minimize the risk of overfitting.

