This protocol describes a prospective, observational, longitudinal cohort study. The observational design improves ecological validity by reflecting real-world patient characteristics; however, it also introduces methodological limitations that must be considered. Due to the non-randomized design and absence of a placebo or untreated control group, confounding variables cannot be fully eliminated, and causal inferences will be limited. Given the observational design, confounding by indication cannot be excluded. Although PAP therapy adherence will be objectively measured, substantial inter-individual variability in use may limit the interpretability of treatment effects. To partly address this limitation, we will perform stratified and regression-based analyses according to PAP therapy adherence levels, enabling us to explore dose–response relationships while adjusting for relevant covariates. The intentionally restrictive inclusion and exclusion criteria may raise concerns regarding both selection bias and feasibility. While these criteria were designed to reduce the influence of major confounding factors and enhance internal validity, they may result in a more selected study population and limit generalizability. However, based on preliminary analyses of patient flow at the study site, recruitment of the target sample size is considered achievable despite these constraints. The comprehensive nature of the study protocol may increase participant burden; however, the majority of assessments are part of routine clinical practice in the evaluation of patients with OSA.

In summary, this study aims to take a comprehensive approach to understanding how PAP therapy may affect cognition in OSA through an extensive assessment of various physiological and pathophysiological mechanisms. Our findings may inform future intervention strategies and improve our understanding of reversible contributors to cognitive decline.

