## Figures and Tables

**Table 1 life-16-00692-t001:** Timeline of the study.

Measures	Study Phase			
	T0. Recruiting and Enrollment	T1. Baseline Assessment	T2. Treatment Period	T3. Follow-Up After 12 Months
Informed consent	X			
Demographic data		X		X
Clinical history		X		X
Neurological, pulmonary, and ENT clinical examinations		X		X
Polysomnography		X		X
Neuropsychological assessment		X		X
Brain MRI with volumetry		X		X
Anthropometric measures		X		X
Blood and saliva sampling		X		X
Gut microbiome from stool		X		X
Vascular functions		X		X
Baroreflex sensitivity		X		X
Adherence to PAP therapy (if applicable)			X	X

Abbreviations: ENT—ear, nose, throat; MRI—magnetic resonance imaging; PAP—positive airway pressure.

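### The cohort can include people never prescribed PAP, but the primary model has a single adherence term, so the hours slope may mix indication with use

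*Protocol article*

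**What the plan says.** Section 2.2 sets the population and the treatment rule: "The study will enroll at least 100 eligible participants with newly diagnosed mild to severe OSA"; "Those patients who are routinely clinically indicated for PAP therapy will receive treatment, and their adherence will be monitored throughout the study"; and "The study protocol does not mandate initiation, modification, or discontinuation of PAP therapy". Section 2.3.1 admits an AHI of 5 or more. Section 2.5.3 ties PAP to the upper part of that range: "The gold standard treatment of moderate/severe OSA is positive airway pressure (PAP) therapy". Table 1 schedules every assessment for the whole cohort at baseline and 12 months but qualifies one row: "Adherence to PAP therapy (if applicable)".

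Other places read as if everyone is treated. Section 2.1 states the longitudinal part of the primary aim as cognitive change following 12 months of PAP, and section 2.5.2 says "After 12 months of PAP treatment, patients will undergo the same assessments as during their initial hospitalization". The Discussion refers to the "absence of a placebo or untreated control group" and concedes that confounding by indication cannot be excluded.

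For the primary model, section 2.7 says "Fixed effects will include time, PAP adherence, and covariates such as age, sex, and education", plus a time × adherence interaction. Section 2.5.3 measures adherence primarily in hours per night and secondarily as adherent versus non-adherent. Neither section gives a value or category for a participant who has no device.

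**The concern.** The exposure in the primary model is defined only for people who have a PAP device, while the cohort is defined more widely. A reader cannot tell whether the time × adherence coefficient describes a dose-response among PAP users or a blend of that with a contrast between indicated and non-indicated patients.

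There are two ways for a never-prescribed participant to meet this model:

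- **Entered at 0 hours.** They share a value with patients who were prescribed PAP and did not use it. Any difference in 12-month cognitive change that comes from severity, or from whatever else drives the indication, then loads on the hours slope.
- **Missing on adherence.** They drop out of the fit. The slope is then not mixed, but the model rests on fewer people than planned, and the only participants who repeat the battery without ever being prescribed PAP contribute nothing.

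The second matters because section 2.5.2 repeats the same battery, so the pre-post change includes any retest gain.

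**Working it through.** **1. The plan's own figures (section 2.6).** A two-sided paired t-test with d = 0.5, α = 0.05 and 80% power gives n = 34 (exact power 0.808), and 34/0.85 = 40. The omnibus test with f² = 0.15 and four predictors gives N = 85 (power 0.803), and 85/0.85 = 100. All of these reproduce. The sample-size arithmetic is not at fault, and about 85 completers is the right working number.

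**2. Never-prescribed entered at 0 h.** The article gives no share untreated and no expected use, so these are assumptions: share p from 10% to 40%; treated use with mean m = 4.5 h and SD s = 2 h; a difference δ = 0.3 SD in 12-month change between indicated and non-indicated patients for reasons unrelated to PAP; and no true effect of hours.

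- Between-group variance of hours = p(1−p)m²
- Within-group variance of hours = (1−p)s²
- Slope bias = δ·m·p(1−p) / [p(1−p)m² + (1−p)s²]

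At p = 0.30, the between part is 0.21 × 20.25 = 4.25 and the within part is 0.70 × 4 = 2.80, total 7.05. The between-group share is 4.25/7.05 = 60%. The bias is 0.3 × 4.5 × 0.21/7.05 = 0.040 SD per hour, and 0.040 × 4.5 = 0.18 SD at mean use.

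| Share never prescribed | Share of variance in hours that is between groups | Bias, SD per hour | Bias at 4.5 h, SD |
|---|---|---|---|
| 10% | 34% | 0.022 | 0.10 |
| 20% | 50% | 0.034 | 0.15 |
| 30% | 60% | 0.040 | 0.18 |
| 40% | 67% | 0.045 | 0.20 |

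The bias is proportional to δ and is zero at δ = 0.

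A simulation (4,000 runs, 85 completers, treated hours limited to 0–8, no true effect of hours) shows what this does to the test. For shares of 10–40%, the pooled slope is falsely significant in 7–15% of runs when δ = 0.25 SD and in 11–45% when δ = 0.5 SD, against a nominal 5%. With δ = 0 the rate stays at about 5%. Fitted to prescribed patients only, the slope is unbiased and the rate is about 5% throughout.

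**3. Never-prescribed missing on adherence.** At 30%, 85 × 0.70 = 59.5, so about 60 remain. Power for the f² = 0.15 four-predictor test falls from 0.80 to 0.62. Section 2.6 ties that calculation to secondary analyses. Paired-test power at d = 0.5 with 60 people is still 0.97.

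**4. What the never-prescribed group could tell us.** A retest gain of 0.2 or 0.3 SD of change, with no PAP effect, would make a pre-post test on 85 completers significant in 45% or 78% of trials. A reference is therefore useful, but this one would be imprecise:

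| Share | Completers | 95% CI half-width for mean change, SD | Power for a 0.5 SD difference in change |
|---|---|---|---|
| 10% | 8 | 0.84 | 27% |
| 20% | 17 | 0.51 | 45% |
| 30% | 26 | 0.40 | 57% |
| 40% | 34 | 0.35 | 62% |

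**The case against.** The strongest reply is that this is a derivation rule. How to code people without a device is commonly left to an analysis plan, and the covariate list in section 2.7 is open-ended, so a severity term or PAP indicator is not ruled out. That stands in part, because the article commits to neither coding. But it does state the primary exposure and the main model terms, and a single adherence term entered at 0 h cannot separate prescription from use.

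A reader might infer that the Discussion flatly contradicts section 2.2 by denying that untreated participants exist. The text does not support that. Next to the mention of a non-randomized design, "absence of a placebo or untreated control group" plausibly means that no comparator was designed, and a cohort can hold incidental untreated patients without one. The firmer mismatch is between sections 2.1 and 2.5.2 on one side and section 2.2 and Table 1 on the other.

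A reader might also infer that confounding by indication went unnoticed. The Discussion concedes it, limits causal claims, and plans stratified and regression analyses by adherence level with covariate adjustment. What remains is that grouping by adherence does not distinguish never-prescribed from prescribed and unused.

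Finally, it is tempting to say that the aim goes unanswered under either coding, or that PAP-minus-non-PAP change should replace the pre-post change. Neither follows. If never-prescribed participants drop out, the model still addresses change and dose-response among PAP users. And a treated-versus-untreated contrast is itself confounded by indication. Nor are the never-prescribed the only information on change near zero hours: section 2.8 keeps participants who discontinue PAP in the analysis.

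**Conclusion.** The point holds in a limited form. The article allows for participants never prescribed PAP, describes follow-up in places as if all were treated, and names a primary model that does not say how those participants enter. If they enter at 0 h, the dose-response slope mixes indication with use, by about 0.02–0.045 SD per hour (0.10–0.20 SD at 4.5 h) under the stated assumptions. If they are missing, the slope is not mixed, and the cost is a smaller model and lost retest information.

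The size rests wholly on assumed inputs. The never-prescribed share is implied rather than counted, and could be small. The bias should not be read as a fraction of the planned d = 0.5, because that figure is a pre-post change and this is a slope across adherence. This should be fixed, with medium confidence. No view is taken on who should receive PAP.

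**What to change.** - **Wording.** Reconcile sections 2.1 and 2.5.2 with section 2.2 and Table 1, and say in the Discussion whether the absent untreated group means a designed comparator.
- **Primary model.** Add PAP prescribed (yes/no) and its interaction with time. Centre hours among prescribed patients and set them to 0 for the never-prescribed, so that the hours × time slope is estimated from prescribed patients only.
- **Severity.** Add baseline AHI and AHI × time. The interaction is needed because a main effect alone does not adjust the change over time.
- **Categorical analysis.** Keep never-prescribed as a category separate from non-adherent.
- **Reporting.** Give the never-prescribed group's 12-month change, and the PAP-versus-non-PAP difference, as a descriptive and confounded benchmark for retest effects. Show it beside the pre-post change, not in its place.

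The cost is some wording and a few extra model terms on data already being collected. The drawback is an imprecise benchmark if few are untreated (about 8–34 completers at 10–40%), which the report should state. The change should be made before the 12-month data are analysed.

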### 2.5. Outcome Measures

#### 2.5.1. Primary Outcome Measures

##### Cognitive Function

The primary outcome of the study is cognitive function assessed by a comprehensive neuropsychological battery. Primary cognitive outcomes will be derived from test performance across the main cognitive domains including memory, executive functions, attention, language, and visuoconstructional abilities. Cognitive performance will be evaluated both cross-sectionally at baseline, to characterize the prevalence, severity, and pattern of cognitive deficits in patients with OSA, and longitudinally as change in cognitive performance from baseline to 12 months. PAP therapy adherence will be treated as an exposure variable in analyses of longitudinal cognitive change.

To improve comparability across tests and reduce measurement variability, standardized z-scores will be calculated for each neuropsychological measure and subsequently aggregated into domain-specific composite scores. In addition to statistical significance, cognitive outcomes will also be evaluated for clinical relevance. Clinically meaningful improvement will be defined as a change greater than 1 standard deviation (SD) from baseline in domain-specific scores or a shift from impaired to normative performance range (e.g., from ≤5th percentile to >15th percentile) [22]. This ensures that changes in test performance reflect not only statistical but also functional significance.

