### 2.8. Data Collection and Management

Upon enrollment, each participant will be assigned a unique study ID to ensure pseudonymization of personal data. The data in this trial will be collected using traditional print-based case report forms. All data entries will be manually transcribed into the electronic system by trained study personnel. Double data entry will be employed to minimize transcription errors and ensure accuracy. The data storage is achieved using an electronic data capture system (REDCAP) which is HIPAA-compliant and allows storage of data in password-protected files in the cloud. Data acquired in paper form are kept in locked files at the respective study site. Only project staff will have access to the trial dataset. Participants who discontinue PAP therapy or deviate from the protocol will remain in the analytical sample, and all data collected up to the time of discontinuation, including cognitive, clinical, and physiological measures, will be included in the analyses.

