## Appendix A

**Table A1 life-16-00692-t0A1:** Neuropsychological test battery for the assessment of OSA patients.

Test	Description	Time of Completion
Rey auditory—verbal learning test	A neuropsychological measure of verbal episodic memory, encompassing immediate recall, learning across trials, delayed recall, and recognition. Participants hear a list of 15 words across multiple trials and are asked to recall them immediately and after a delay [25].	15–20 min
Figure copy task	A visuoconstructional task from the Czech short neuropsychological battery. The subject is asked to precisely copy a geometric figure presented on a stimulus sheet. Administered twice (initial and retest) to assess visual perception, spatial planning, and memory [26].	5–10 min
Controlled oral word association test	A verbal fluency task requiring rapid generation of words beginning with specified letters (K—P—S for Slovak population). It assesses phonemic fluency, executive function, and lexical retrieval [27,28].	5 min
Category fluency test	A semantic fluency measure where subjects list as many words from a given category (e.g., animals) in one minute. It evaluates semantic memory and executive retrieval processes [27,28].	5 min
Trail making test	A two-part test evaluating processing speed, visual search, attention, and task-switching. Part A connects numbered dots; Part B alternates between numbers and letters [29].	5–7 min
Stroop color and word test	The stroop color and word test is a widely used neuropsychological measure of selective attention, processing speed, cognitive flexibility, and inhibitory control. In its classic form, participants complete three tasks: word reading, color naming and naming the ink color of color-words printed in an incongruent color (e.g., the word “RED” printed in blue ink), requiring the participant to inhibit the automatic tendency to read the word [30].	5 min
Digit span	A working memory test comprising forward and backward recall of digit sequences. Assesses attention, concentration, and short-term memory [31].	5 min
Montreal cognitive assessment (MoCA)	A 30-point screen for mild cognitive impairment targeting attention, executive function, memory, language, visuospatial abilities, and orientation [32].	10 min
Generalized anxiety disorder 7-item scale (GAD—7)	A 7-item self-report questionnaire to screen and assess the severity of generalized anxiety disorder. Items are rated on a 4-point scale [33].	3 min

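### The plan rules out blinding of investigators without exception, although its stated reason does not prevent keeping PAP status and adherence data from the 12-month cognitive examiner and scorer.

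*Protocol article*

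**What the plan says.** Section 2.2 (Study Design and Setting) takes a position on masking: "Blinding of participants and investigators to PAP therapy status is not feasible due to the nature of the study design". No other section describes masked testing or masked scoring.

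Section 2.5.1 defines the outcome: "The primary outcome of the study is cognitive function assessed by a comprehensive neuropsychological battery". Section 2.4.2 and Appendix A list the tests: verbal learning, letter and category fluency, Trail making, Stroop, digit span and figure copy. In the verbal learning test, for example, "Participants hear a list of 15 words across multiple trials and are asked to recall them immediately and after a delay".

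Section 2.5.1 also fixes the role of adherence: "PAP therapy adherence will be treated as an exposure variable in analyses of longitudinal cognitive change". Section 2.7 puts it in the primary model: "An interaction term between time and adherence will be used to assess whether longitudinal changes differ according to adherence level".

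The exposure comes from a separate source. Section 2.5.3 says: "Adherence to the treatment will be measured through an adherence tracking system using smart memory cards". Section 2.8 describes paper case report forms with double data entry, and "each participant will be assigned a unique study ID to ensure pseudonymization of personal data".

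**The concern.** The reason given in section 2.2 is narrower than the conclusion drawn from it. Patients know whether they use PAP and their clinicians prescribe it, so neither can be masked. Whether the person who tests or scores at 12 months is told about PAP use is a matter of organisation, and an observational design leaves it open.

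An examiner who knows that a participant used PAP well, or hardly at all, may be more or less generous in timing, in accepting a response or in judging a drawing. An error of that kind is linked to adherence, so it enters the time×adherence term. The named covariates (age, sex and education) cannot remove it, because the error arises in the measurement itself.

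The limitations in the Discussion cover confounding by indication, the absence of an untreated control group and variable PAP use. Unmasked assessment is not among them.

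**Working it through.** **1. Does the stated reason cover the examiner and scorer?**

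| Element | Where | What follows |
|---|---|---|
| PAP given on routine indication, no randomisation | 2.2 | Participants and treating clinicians know PAP status |
| Adherence read from device memory cards | 2.5.3 | The data need not pass through the test session |
| Paper forms, study ID, double entry | 2.8 | Scores can be entered and locked under the ID before a merge |
| Cognitive testing and adherence both marked at the 12-month visit | Table 1 | Both kinds of information arise at one visit, and no rule separates them |

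The design reason covers the first row only.

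**2. Which parts of the primary outcome are exposed?**

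- *Baseline profile.* Sections 2.3.1 and 2.3.2 require newly diagnosed OSA and no earlier OSA therapy. No adherence exists yet, so knowledge of it cannot influence baseline scores.
- *Change over 12 months by adherence.* The follow-up score is obtained after PAP use has become known. A scoring shift related to use goes into the time×adherence term of section 2.7.

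**3. The plan's own sample-size figures (section 2.6).**

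- Paired *t*-test, d = 0.5, two-sided α = 0.05: n = 34 (power 0.808), and 34/(1 − 0.15) = 40.
- Regression, f² = 0.15, four predictors, 80% power assumed: n = 85 (power 0.803), and 85/(1 − 0.15) = 100.

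All of these reproduce. Masking changes none of them.

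**4. Illustration of size, on assumed inputs.**

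The document gives no bias size and no adherence group sizes. Assume about 85 completers split evenly, so 42 per group, no true effect, and a differential scoring shift of *b* SD of the change score. For a two-sided two-sample *t*-test at 5%:

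- degrees of freedom = 2 × 42 − 2 = 82, critical value 1.989
- noncentrality λ = b × √(42/2) = b × 4.583
- rejection probability = P(|T| > 1.989), where T is noncentral *t* with 82 degrees of freedom and noncentrality λ

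| b (assumed) | λ | False-positive rate |
|---|---|---|
| 0 | 0 | 0.050 |
| 0.1 | 0.458 | 0.074 |
| 0.2 | 0.917 | 0.148 |
| 0.3 | 1.375 | 0.274 |

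In general λ = b × √(n₁n₂/(n₁ + n₂)). For a given total this is largest at an even split, so an uneven split would give lower rates. Section 2.5.3 makes adherence primarily continuous, with the two-group split secondary. The table therefore shows how sensitive a comparison by adherence could be and does not describe the planned primary model.

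**The case against.** The strongest reply has four parts.

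- **The sentence concerns PAP therapy status, and the article does not say who tests or scores.** It is fair that a condensed article may leave such detail to the full protocol. A reader might infer that the plan calls masking to adherence data infeasible. It does not; on adherence data it is silent. What stands is that the sentence on status is a stated position covering investigators without exception, and the reason given does not support that breadth.
- **Adherence is not the whole primary question.** This is correct. Section 2.1 makes the cognitive profile and its 12-month change the primary aim and places the relation to adherence among the exploratory aims. A reader might infer that the entire primary result is at risk. The baseline part is not. The adherence term is nevertheless in the primary longitudinal model of section 2.7.
- **The tests are structured performance measures given in a standardised order.** This limits the bias. It does not remove it where the examiner times a task, accepts a word or judges a figure.
- **Masking would be partial.** Participants may mention their PAP use, and an examiner may learn of it in other ways at a visit that repeats all the assessments. This stands, and it is a reason to record unmasking.

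Two further inferences are not supported. One is that masking needs no extra staff: the document does not say who tests, who scores or who reads the cards. The other is to express an assumed shift as a share of d = 0.5: in section 2.6 that figure is a within-subject effect, whereas the shift is a difference between groups in change.

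**Conclusion.** The point holds in a limited form. Section 2.2 declares blinding of investigators infeasible for a reason that applies to participants and treating clinicians only. The 12-month cognitive scores are partly examiner-dependent, and the time×adherence term would absorb any scoring shift linked to known PAP use. The Discussion does not acknowledge this.

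Nothing in the document shows that such a shift will occur, and its size cannot be derived. The range of about 7% to 27% in place of 5% rests wholly on assumptions: 42 per group, no true effect, a two-group comparison, and a differential shift of 0.1 to 0.3 SD of change. The baseline aim and the sample size are unaffected.

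**What to change.** In section 2.2, limit the infeasibility statement to participants and treating clinicians. Then state that:

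- the examiner and scorer of the 12-month battery are not given PAP status or memory-card data;
- forms are scored under the study ID;
- scores are entered and locked before adherence data are merged;
- any unmasking of the examiner or scorer is recorded.

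If roles at the site do not allow this, list unmasked cognitive assessment as a limitation in the Discussion.

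The main change is in the order of data handling; the model and the sample size stay as they are. Roles may have to be reassigned if one person now tests, scores and reads the cards, and masking will be incomplete because some participants will reveal their PAP use.
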